**ACRONYMS and ABBREVIATIONS**

AE Adverse event

CRF Case report form

FDA Food and Drug Administration

FVC Forced vital capacity

GCP Good clinical practice

ICH International Conference on Harmonization

IRB/IEC Institutional Review Board/Independent Ethics Committee

MHFMS Modified Hammersmith Functional Motor Scale

NERI New England Research Institutes

OHRP Office for Human Research Protections

SAE Serious adverse event

SMA Spinal Muscular Atrophy

SMN Survival motor neuron (gene or protein)

| **Pilot Study of Biomarkers** **for Spinal Muscular Atrophy**  **(BforSMA)** |
| --- |

**SYNOPSIS**

**RATIONALE**

Spinal Muscular Atrophy (SMA) is one of the two most common inherited children’s neuromuscular disorders. There currently is no cure and there are no therapeutics approved to slow progression of the disease. SMA is characterized by a loss of alpha motor neurons in the spinal cord, severe atrophy of proximal muscles and progressive debility and disability due to respiratory, gastrointestinal and functional complications of the disease.

Though SMA is a relatively common orphan disease, recruitment of patients for the number of candidate therapies is expected to become rate-limiting for the development of therapeutics. A biomarker is a characteristic that is objectively measured and evaluated, and is an indicator of a pathologic process. The goal in biomarker identification is an empiric interim readout that is directly related to clinical endpoints, i.e., a surrogate endpoint for disease progression and/or treatment effect. The potential advantages of a quality biomarker of disease severity or a network of biomarkers are manifold:

- May replace a distal endpoint with a proximal endpoint, potentially shortening the development time of new therapeutic modalities.
- May be measured more frequently and easily.
- May have greater precision.
- May increase the measured dynamic range of a disease process or treatment effect compared to clinical metrics.
- May result in reduced sample size requirements for clinical studies.
- May lead to expedited decisions concerning the validity of therapeutic interventions.

Thus, the development of biomarkers will have important implications in therapeutics development timelines and more efficiently allocate patient resources into studies with the greatest probability of success.

The goal of this pilot study is to identify a marker or panel of markers in the blood or urine from a wide range of SMA patients that segregates with measures of clinical severity. From this identification of candidate biomarkers, it is hoped that further investigations, both longitudinal natural history and clinical efficacy studies, will verify a biomarker with the sensitivity and specificity that will allow its eventual use as a validated pharmacodynamic marker or surrogate endpoint. In addition, this effort may elucidate biological pathways that may be potential therapeutic targets.

**STUDY DESIGN**

This study will be a multi-center, pilot study enrolling 120 subjects, age 2 to 12 years. The study will enroll subjects from approximately 15 academic pediatric neuromuscular clinics.

Three groups of SMA patients and one cohort of control children will be enrolled according to the classifications below:

- Children with type I SMA (n=15).
- Children with type II SMA (n=45).
- Children with type III SMA (n=40).
- Control children (n=20) will match the gender and age distribution expected in the SMA cohorts. Control children may be either confirmed non-carrier, genetically- related siblings of SMA children or unrelated children.
  - n=5 Females age 2-5.
  - n=5 Females age 6-12.
  - n=5 Males age 2-5.
  - n=5 Males age 6-12.

Each subject will be seen for a single visit, during which an assessment of functional ability, pulmonary status and nutritional status will be performed. In addition, blood and urine specimens will be collected for biomarker assessment and DNA specimens collected for SMN2 copy number. SMN1 genotyping will be conducted for unrelated control subjects only. No therapeutic intervention will occur.

**STUDY OBJECTIVES**

**Primary:**

- To identify candidate blood and urine biochemical markers that correlate with disease severity as determined by the Modified Hammersmith Functional Motor Scale across a range of type I, type II and type III children with Spinal Muscular Atrophy (SMA) (1).

**Secondary:**

- To determine if there are biomarkers from types I-III SMA patients that correlate with SMA type, age at disease onset, 10-meter Timed Walk Test (ambulatory subjects only), pulmonary function, nutritional assessment, SMN protein level, SMN transcript level or SMN2 copy number.
- To determine if identified candidate biomarkers are associated with the disease state through comparison of SMA specimens with control volunteer specimens.
- To determine if there are potential biochemical pathways that may represent targets for therapeutic intervention in SMA.

**KEY INCLUSION CRITERIA**

For all groups:

- Age 2 to 12 years, inclusive.
- In good health in the judgment of the clinical investigator at the time of assessment.

Specific group requirements – SMA children:

- Documented homozygous deletion of SMN1 (exon 7).
- SMA type I defined as the inability ever to sit unaided in the judgment of the clinical investigator.
- SMA type II defined as the ability to ever sit unaided for >30 seconds on a flat surface in the judgment of the clinical investigator.
- SMA type III defined by the ability to ever stand unaided for 30 seconds and walk unaided for >30 ft.

Specific group requirements – Control children:

- Otherwise healthy children that may be either genetically-related siblings of SMA children (confirmed non-carriers) or unrelated children.

**KEY EXCLUSION CRITERIA**

For all groups:

- Systemic or specific-organ illness, including renal, hepatic, cardiac, pulmonary, significant gastrointestinal illness, hematologic or rheumatic disorders requiring ongoing treatment or chronic medication use.
- Any known genetic condition other than Spinal Muscular Atrophy requiring pharmaceutical treatment.
- Use of any putative SMN-enhancing medications or treatments for 14 days prior to enrollment including, valproic acid, phenylbuterate, and hydroxyurea.
- Use of carnitine, creatine, oral albuterol and riluzole for 14 days prior to enrollment.
- Use of any oral prescription medications for 14 days prior to enrollment with the exception of the following medications, which are allowed: anti-reflux medications (e.g. rantidine), constipation or stool softening medications (e.g. polyethylene glycol 3350), stool bulking agents, and inhaled bronchodilator medications and nebulizers (e.g. albuterol).
- Any illness requiring treatment with antibiotics or anti-inflammatory medication within the past 14 days.
- Participation in a clinical trial (except observational studies) within the previous 14 days.

**STUDY EVALUATIONS**

At time of enrollment, the Principal Investigator or designee will obtain detailed clinical history including age of disease onset, diagnosis, motor milestones, loss of motor function (sitting, ambulation). A standardized general physical examination will be performed including vital signs, inspection and evaluation of nutritional balance, pulmonary function and neurological examination.

Nutritional assessment by site P.I. or designee:

- Height, weight, triceps skin fold thickness, and ulnar length.
- Nutritional status question.

Motor function assessment:

- Modified Hammersmith Functional Motor Scale.
- 10-meter Timed Walk Test (ambulatory subjects only).

Pulmonary assessment

- Standardized question about level of respiratory support.
- Forced Vital Capacity (FVC) when > 5 years.

Specimen acquisition

- Blood collected for mRNA, proteomic and metabolomic analysis.
- DNA to determine SMN2 copy number.
- DNA to determine SMN1 genotyping (non-genetically related controls only).
- Non-first morning void urine for proteomic and metabolomic analysis.

**RATIONALE FOR NUMBER OF SUBJECTS**

- The number of subjects was selected based on clinical and statistical considerations.
- The sample size for the SMA subjects was selected to achieve 83% power for the primary outcome of Modified Hammersmith Functional Motor Scale, using an elastic net regression analysis, assuming a 0.75 correlation between the observed and theoretical outcomes. The power estimate is based on an average of 100 simulated datasets using data available from the original Hammersmith Scale.
- The sample size of 20 control subjects was selected to achieve at least 90% power to detect a univariate biomarker with a mean-fold change (MFC) of 1.5 when the false discovery rate is controlled at 0.05.
- In both power calculations it was assumed that 10% of profiled analytes are true biomarkers, and that variance of analytes is equal to 0.2.

# INTRODUCTION

- 1. Background Information

Spinal muscular atrophy (SMA) is a common and severe autosomal recessive disease, affecting all races with an overall incidence in the United States that rivals cystic fibrosis and sickle cell disease (2).

SMA manifests across a continuous spectrum of severity and age of disease onset that has been divided into four groups: type I (severe infantile acute SMA, or Werdnig-Hoffmann disease); type II, (infantile chronic SMA); type III (juvenile SMA, or Wohlfart-Kugelberg-Welander disease); and type IV (adult-onset SMA). The three most severe forms manifest in children, and are divided by maximal motor function achieved: type I infants never sit, type II sit, but never walk, and type III are able to walk at least for a short time (3). All types are caused by homozygous protein-null mutations (deletion, conversion, or missense) of the SMN1 gene (4).

Across its range of manifestation, the common clinical feature of SMA is diffuse, symmetric weakness and atrophy of skeletal muscle due to denervation. This is caused by degeneration of the anterior horn cells (motor neurons) of the spinal cord and brainstem. The understanding of SMA has expanded greatly since the discovery of the genetic basis. In humans a large region of chromosome 5q is duplicated, with the result that two copies of SMN reside on each chromosome. In addition, there is considerable meiotic instability of the SMN-critical 5q duplicated chromosomal region owing to differences in number, copy number, and orientation of multiple markers (5). The two copies of SMN – designated SMN1 and SMN2 – differ in only one base pair, a synonymous protein-coding change in exon 7 (6). Most SMN protein is derived from the SMN1 gene, but the SMN2 gene contributes a small amount of normal SMN protein due to a leaky splice site at the intron 6-exon 7 boundary. If SMN1 is lost on both alleles, the protein translated from SMN2 is sufficient to rescue embryonic lethality, but insufficient to prevent manifestation of the SMA syndrome. The range of clinical severity observed in SMA varies in part as a consequence of variation in copy number of SMN2: greater copy number is associated with a more mild phenotype (7).

SMN is expressed in all tissues and cell types; the relative specificity of the pathogenic process for lower motor neurons is not currently understood. Αlpha motor neurons may have unique susceptibility to a loss in snRNA assembly or SMN may have accessory functions in this cell or its connections (8) (9) (10). SMN protein is found in axons and growth cones (11) (12), and may function to transport mRNAs from the nucleus to synapse. In other models it is localized post-synaptically at the neuromuscular junction and within the Z-bands of striated muscle (13). Therefore the primary pathophysiology of SMA may stem not only from functions within the cell body of the lower motor neuron, but also within the axon, neuromuscular junction or even muscle.

Technology now allows non-assumptive data mining of the human nucleic acid (genome and transcriptome), polypeptide (proteome) and small molecule (metabolome) repertoire. A functional consequence is that this technology can be used to generate a disease ‘signature’ of biochemical markers which segregates with disease process or severity. Because these biochemical changes are assumed to be a consequence of the single gene perturbation in SMA, presumptive markers may mirror the disease pathology. This has important consequences in therapeutics discovery for SMA:

1. It may lead to the generation of sensitive disease biomarkers that are functional surrogates for disease progression and/or therapeutic benefit.
2. It may lead to identification of previously unidentified targets or pathways critical in the manifestation of the disease.
3. It may support hypotheses of pathogenesis that confirm and/or extend our knowledge of the disease process.
   1. Study Rationale

Clinical testing of new therapeutics in SMA requires effective tools for recruiting patients and measuring outcomes pertinent for registration. Because of many variables including age of disease onset and a broad spectrum of severity, no one clinical outcome measure currently represents the gold standard for clinical testing (14). We propose that there may be a biochemical surrogate of disease that may represent a more sensitive and uniformly applicable variable to measure as an interim readout or surrogate endpoint. This pilot protocol is intended to preliminarily identify a panel of biochemical markers that segregate with disease severity as judged by several diagnostic and outcome metrics.

A biomarker is a characteristic that is objectively measured and evaluated, and is an indicator of a pathologic process. The goal in biomarker identification is an empiric interim readout that is directly related to clinical endpoints, i.e., a surrogate endpoint for disease progression and/or treatment effect. The potential advantages of a quality biomarker of disease severity or a network of biomarkers are manifold:

1. May replace a distal endpoint with a proximal endpoint, potentially shortening the development time of new therapeutic modalities.
2. May be measured more frequently and easily.
3. May have greater precision.
4. May increase the measured dynamic range of a disease process or treatment effect compared to clinical metrics.
5. May result in reduced sample size requirements for clinical studies.
6. May lead to expedited decisions concerning the validity of therapeutic interventions.

Thus, the development of biomarkers will have important implications in therapeutics development timelines and more efficiently allocate patient resources into studies with the greatest probability of success.

The goal of this pilot study is to identify a marker or panel of markers in the blood or urine from a wide range of SMA patients that segregates with measures of clinical severity. From this identification of candidate biomarkers, it is hoped that further investigations, both longitudinal natural history and clinical efficacy studies, will verify a biomarker with the sensitivity and specificity that will allow its eventual use as a validated pharmacodynamic marker or surrogate endpoint. In addition, this effort may elucidate biological pathways that may be potential therapeutic targets.

# OBJECTIVES

- 1. Primary Objective
- To identify candidate blood and urine biochemical markers that correlate with disease severity as determined by the Modified Hammersmith Functional Motor Scale across a range of type I, type II and type III children with spinal muscular atrophy (SMA).
  1. Secondary Objectives
- To determine if there are biochemical markers from types I-III SMA patients that correlate with SMA type, age at disease onset, 10-meter Timed Walk Test (ambulatory subjects only), pulmonary function, nutritional assessment, SMN protein level, SMN transcript level, or SMN2 copy number.
- To determine if identified candidate biomarkers are associated with the disease state through comparison of SMA specimens with control volunteer specimens.
- To determine if there are potential biochemical pathways that may represent targets for therapeutic intervention in SMA.

# STUDY DESIGN

This study will be a multi-center, pilot study enrolling 120 subjects, age 2 to 12 years from approximately 15 academic pediatric neuromuscular clinics. Primary care pediatric practices within these institutions may refer patients for the controls. Participating clinic sites will have the laboratory support to process the blood and urine samples appropriately for shipment to central laboratory and biomarker analysis.

Each subject will be seen for a single visit, during which an assessment of functional ability, pulmonary status and nutritional status will be performed. In addition, blood and urine specimens will be collected for biomarker assessment and DNA specimens collected for SMN2 copy number. SMN1 genotyping will only be conducted on control subjects who are genetically unrelated to SMA children. Control subjects have the option to decline the DNA (SMN1 gene analysis) portion of the study. No therapeutic intervention will occur.

# STUDY POPULATION

Three groups of SMA patients and one cohort of control children will be enrolled according to the classifications below:

- Children with type I SMA (n=15).
- Children with type II SMA (n=45).
- Children with type III SMA (n=40).
- Control subjects (n=20) will match the gender and age distribution expected in the SMA cohorts. Control children may be either confirmed non-carrier, genetically- related siblings of SMA children or unrelated children (limit 1 child per family for enrollment in the control cohort).
- n=5 Females age 2-5.
- n=5 Females age 6-12.
- n=5 Males age 2-5.
- n=5 Males age 6-12.
- SMA subjects will be enrolled from approximately 15 academic pediatric neuromuscular clinics.
- Control subjects will be enrolled from pediatric neuromuscular clinics as well as referring pediatric practices within the same institutions.
  1. Inclusion Criteria

For all groups:

1. Age 2 to 12 years, inclusive.
2. In good health (other than SMA) in the judgment of the clinical investigator at the time of assessment.

SMA group requirements:

1. Documented homozygous deletion of SMN1 (exon 7). Genotyping results must be performed by a CLIA certified laboratory and documented via chart review.
2. SMA type I defined as the inability ever to sit unaided in the judgment of the clinical investigator.
3. SMA type II defined as the ability to ever sit unaided for >30 seconds on a flat surface in the judgment of the clinical investigator.
4. SMA type III defined by the ability to ever stand unaided for 30 seconds and walk unaided for >30 ft in the judgment of the clinical investigator.

Control group requirements:

1. Otherwise healthy children that may be either genetically-related siblings of SMA children (genetically confirmed non-carriers), or unrelated children. Only one sibling per family with an SMA subject may be enrolled (includes related and unrelated siblings).
   1. Exclusion Criteria

For all groups:

1. Systemic or specific-organ illness, including renal, hepatic, cardiac, pulmonary, significant gastrointestinal illness, hematologic or rheumatic disorders requiring ongoing treatment or chronic medication use.
2. Any known genetic condition other than Spinal Muscular Atrophy requiring pharmaceutical treatment.
3. Use of any putative SMN-enhancing medications or treatments for 14 days prior to enrollment including, valproic acid, phenylbuterate, and hydroxyurea.
4. Use of carnitine, creatine, oral albuterol or riluzole for 14 days prior to enrollment
5. Use of any oral prescription medications for 14 days prior to enrollment with the exception of the following medications, which are allowed: anti-reflux medications (e.g. rantidine), constipation or stool softening medications (e.g. polyethylene glycol 3350), stool bulking agents, and inhaled bronchodilator medications and nebulizers (e.g. albuterol).
6. Any illness requiring treatment with antibiotics or anti-inflammatory medication within the past 14 days.
7. Any rash (excluding diaper rash or eczema) requiring treatment within the past 7 days.
8. **Any severe asthma attack requiring treatment with oral or parenteral steroids within the past 7 days.**
9. Any fever over 100 degrees Fahrenheit or 38 degrees Celsius within the past 7 days.
10. Any immunization within the past 7 days.
11. Any injury sustained that resulted in a bone fracture or needed stitches within the past 7 days.
12. Any surgery **within the past 7 days.**
13. **Any receipt of anesthesia within the past 7 days.**
14. **Any Emergency Room visit within the past 7 days.**
15. **Any hospitalization within the past 7 days.**
16. Any stomach illness with vomiting within the past 7 days.
17. **Any migraine headache within the past 7 days.**
18. Participation in a clinical trial (except observational studies) within the previous 14 days.

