1. Medical history including motor milestones, age of disease onset for children with SMA, loss of motor function (sitting, ambulation) for children with SMA.
2. Physical Examination including Neurological assessment ,vital signs: sitting BP, pulse and respirations and height, weight and ulnar length.
3. Nutritional assessment by Principal Investigator or designee:
4. Triceps skin fold thickness.
5. Nutritional status question about level of solid food intake.
6. Motor function assessment
7. Modified Hammersmith Functional Motor Scale.
8. 10-meter Timed Walk Test (ambulatory subjects only).
9. Pulmonary assessment
10. Standardized question about level of respiratory support.
11. Forced Vital Capacity (FVC) when subject is greater or equal to 5 years.
12. Specimen acquisition
13. Blood collected for mRNA, proteomic and metabolomic analysis.
14. DNA to determine SMN2 copy number.
15. DNA to determine SMN1 genotyping (genetically unrelated controls only). Subjects have the option to decline this test.
16. Blood collected for SMN protein level.
17. Non-first morning void urine for proteomic and metabolomic analysis.

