In order to find disease-specific biomarkers, comparison of biomarkers between SMA and control cases will be performed using regression analysis, controlling for sex and age. Correlations of biomarkers with outcomes will be conducted within SMA cases, as well as in the combined population of SMA and control cases.

To model the correlation of each individual biomarker with the Modified Hammersmith Functional Motor Scale, univariate regression analyses will be performed, controlling for sex and age. Additionally, elastic net multivariate regression (25) will be used to find a composite set of biomarkers that correlates with outcome.

Univariate regression and elastic net multivariate regression will also be used for continuous secondary outcomes (e.g., age of disease onset, height, weight). For categorical outcomes (e.g., SMA type), analysis of variance (ANOVA), controlling for sex and age, will be performed to discover individual biomarkers that vary by outcome. Likewise, PAM (Prediction Analysis of microarrays) (26) will be used to try to find a composite set of biomarkers that varies by outcome.

In all analyses a p-value ≤ 0.05 will be considered statistically significant. The false discovery rate (27) will also be controlled. If there is an extensive amount of missing data, or data appears not to be missing completely at random, then multiple imputations will be considered. Standard statistical software packages (e.g., SAS) will be used.

- 1. Interim Analysis

No interim analysis for safety or efficacy will be performed during this study.

- 1. Potential Risks and Benefits

Potential risks to study subjects are minimal. Blood will be drawn in volumes that are approximately half (or less than half) of the maximum blood draw allowed for children (by weight) (28) (29). SMN2 copy number will be genotyped from DNA specimens for all cohorts. SMN1 gene analysis will only be done on those control subjects with no genetic relationship to SMA children. SMA subjects will be pre-diagnosed and therefore no further risks are anticipated from a genetic point of view. The control subjects may opt out of the DNA portion (SMN1 gene analysis) of the study. The control subject’s risk is that the study does not benefit the individual directly.

Potential benefits are that study subjects will benefit from the satisfaction that they are participating and contributing to SMA research.

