The risk/benefit ratio is favorable since participation in the study is reasonably commensurate to routine care for an SMA subject over the course of one visit.

- 1. Limitations of the Study

Several limitations were considered in the design of the study.  Outlined below is how the study proposes to mitigate these limitations:

1. Biomarkers may vary by age and Type I subjects will be on the younger end of the age distribution.  The proposed solution is to control for age in all statistical models.
2. Based on the inclusion criterion for age, the study outcomes may not be generalization to children <2 or >12 years old. The primary outcome is not reliable in children less than 2 years of age. Any putative biomarkers identified in this effort would need to be validated in follow-on studies in a broader age distribution.
3. The sample size selected is based on number of specimens collected and it is possible that less than 100% of specimens collected will be analyzable. The study will allow for replacement of subjects to account for these specimens.
4. There is a potential that differences in standards of care between centers or regional differences (in diet or lifestyle) may have an impact on putative biomarker levels  It is unknown whether this has an effect prior to identification of a biomarker.  An ideal biomarker would be robust against effects of lifestyle and diet. The study design attempts to mitigate this potential effect by instituting site caps by cohort.
5. Recruitment of control children may be difficult as they do not have a direct or indirect benefit (other than siblings) from the study.  It is possible that this will be an issue; however the pool of control children is significantly larger than the SMA pool and therefore 20 control individuals is achievable.

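### Permitted background drugs are not adjusted for or listed for recording, so if their use differs by severity or between SMA and controls, a drug-derived analyte could be reported as a marker

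*Protocol*

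**What the plan says.** **Eligibility (Protocol 4.2).** Item 5 bars oral prescription drugs for 14 days before enrolment, but excepts "anti-reflux medications (e.g. rantidine), constipation or stool softening medications (e.g. polyethylene glycol 3350), stool bulking agents, and inhaled bronchodilator medications and nebulizers (e.g. albuterol"). No washout before sampling is set for these classes. Item 4 separately bars "Use of carnitine, creatine, oral albuterol or riluzole for 14 days prior to enrollment". Item 1 excludes organ illness, pulmonary and significant gastrointestinal illness included, that needs ongoing treatment or chronic medication.

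**Measurement (6.4 and 1.1).** Blood is taken for mRNA, proteomic and metabolomic work. Urine is taken as "Non-first morning void urine for proteomic and metabolomic analysis". Section 1.1 describes the approach as assumption-free and as covering small molecules. The items listed under medical history and the other procedures in 6.4 do not mention medication.

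**Analysis (11.2).**
- Each biomarker against the Modified Hammersmith Functional Motor Scale (MHFMS): "univariate regression analyses will be performed, controlling for sex and age".
- SMA against controls: "comparison of biomarkers between SMA and control cases will be performed using regression analysis, controlling for sex and age".
- SMA type: "analysis of variance (ANOVA), controlling for sex and age, will be performed to discover individual biomarkers that vary by outcome".
- Composite panel: "elastic net multivariate regression (25) will be used to find a composite set of biomarkers that correlates with outcome". This sentence names no covariate.

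**Limitations (11.5).** For age: "The proposed solution is to control for age in all statistical models". The section concedes that differences in standards of care between centres may affect marker levels. The mitigation offered is site caps by cohort, which section 5.2 lifts three months after the first enrolment.

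**The concern.** The permitted classes treat respiratory and gastrointestinal problems, and the Synopsis rationale names complications of both kinds as sources of disability in SMA. It is therefore plausible, though not stated, that use is higher in the weaker children and lower in controls, who must be otherwise healthy. An assumption-free small-molecule screen may pick up a parent drug, a metabolite or an excipient.

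Such an analyte would satisfy the primary objective (correlation with MHFMS) or the disease-state objective (difference from controls) without reflecting the biology of SMA. Sex and age adjustment does not remove it. Site caps act on differences between centres, not on drug use that varies with severity within a centre. Each child is seen once, so exposure that is not recorded at that visit is hard to recover later.

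**Working it through.** The plan states no figure on this point, so the check asks how often an analyte whose only link to severity is drug use would be declared a marker.

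**Inputs from the Protocol.** 15/45/40 children with type I/II/III and 20 controls; 100 analytes, 10% of them true markers, variance 0.2 (11.1); significance at p≤0.05 with FDR also controlled (11.2).

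**Assumed, not in the Protocol.** Drug use by cohort; the shift in users; MHFMS distributions by type (means 1/12/30, SDs 1/7/7); r=0.5 for true markers in the FDR runs.

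**Model.** Analyte = N(0,1) + shift × use, with use drawn as Bernoulli by cohort. Pearson test against MHFMS within SMA; t-test for SMA against controls. The expected SMA-control mean difference is shift × (use in SMA − use in controls).

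Overall SMA use in each setting:
- 50/25/10%: (7.5 + 11.25 + 4)/100 = 22.75%
- 60/30/10%: (9 + 13.5 + 4)/100 = 26.5%
- 40/30/20%: (6 + 13.5 + 8)/100 = 27.5%

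**1. MHFMS, shift of 2-3 SD**

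| Use in I/II/III | p≤0.05, unadjusted | FDR 0.05, 10 true markers | FDR 0.05, no true markers |
|---|---|---|---|
| 50/25/10% to 60/30/10% | 40-74% | 13-40% | 3-17% |
| 40/30/20% | about 15-20% | 3-4% | under 1% |
| equal across types | about 5% | no excess | no excess |

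The FDR result depends on the number of true markers because the Benjamini-Hochberg cut-off for the top-ranked of 100 analytes is 0.05 × 1/100 = 0.0005, whereas behind ten true markers it is 0.05 × 11/100 = 0.0055.

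**2. SMA against controls, p≤0.05, no FDR control**
- Steeper gradients, controls 2-5%: about 17-47%.
- 40/30/20%, controls 5%: 26-37%.
- Flat 25% in every SMA type, controls 5%: 21-30%. At a 2 SD shift the expected difference is 2 × (0.25 − 0.05) = 0.40 SD, with no severity gradient.

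**3. With the planned sex and age adjustment.** A separate run regressed MHFMS on the analyte with sex and age as covariates. It used slightly different assumed MHFMS distributions, SD √0.2 = 0.447 on the natural-log scale, and fold shifts of 1.5 to 4 in users (ln 1.5/0.447 = 0.9 SD to ln 4/0.447 = 3.1 SD). False declarations at p≤0.05:

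| Use in I/II/III | Sex and age only |
|---|---|
| 30/30/30% | 4-5% |
| 40/30/20% | 8-18% |
| 60/30/10% | 19-68% |
| 80/40/10% | 33-91% |

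Adding drug use as a covariate brought every setting back to 4.3-5.6%. Sex and age adjustment therefore does not protect; information on drug use does.

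**The case against.** The strongest objections, and what stands of each:

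- **The premises are not in the document.** A reader might infer that use does rise from type III to type I and that these drugs are measured. The Protocol gives no usage rates and no detection data, and not every class (stool-bulking agents, for example) need be detectable. This stands: the point is conditional.
- **The unadjusted 40-74% ignores the planned FDR control.** This stands; the 3-40% range is the fairer figure. FDR control does not cure the problem, however, because the association would be real in the data but caused by the drug. One pooled use rate is also generous, since any single class would be used less often.
- **Exclusion 1 may lower use.** It may. The Protocol does not spell out how it is to be read with item 5, so the size of the effect is unknown.
- **Drug use may be recorded anyway.** The history list in 6.4 is not exhaustive, and the CRFs and Manual of Operations are not shown. If they capture permitted drugs, only the analysis step is needed. A SAP could add covariates, but 11.2 itself names sex and age, and no SAP can use exposure that was not collected.
- **Candidates will be validated later.** The remark in 11.5 concerns a broader age range, not confounding. A drug trace could replicate in similarly treated children.
- **Albuterol.** Items 4 and 5 might be read as contradicting each other. They do not: one bars the oral form and the other allows inhaled or nebulized forms.

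**Conclusion.** The point holds in conditional form. The Protocol allows four drug classes up to sampling, profiles small molecules in both fluids, fixes sex and age as the covariates of its univariate models, and offers only temporary site caps against differences in care. If use varies with severity or between SMA and controls, and if the assays detect the drug, a drug-derived analyte may be reported as a candidate marker.

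The size rests wholly on assumed use and shift. After FDR control it runs from about 3-40% under a steep gradient to under 5% under a mild one, with no excess for MHFMS under none. The SMA-control comparison needs no gradient within SMA, only lower use in controls.

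These are rates for one affected analyte. A reader might take them as the false-positive rate of the study or of all three assay types. The calculation does not support that: a drug trace in the metabolomic data does not by itself touch the mRNA or proteomic results.

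**What to change.** Leave eligibility unchanged.

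**Section 6.4:** record each permitted drug taken in the 14 days before sampling, by any route, with the time of last dose.

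**Section 11.2:**
1. Report use of each permitted class by SMA type and in controls.
2. Before modelling, remove analytes identified as a permitted drug, its metabolite or an excipient. Covariate adjustment alone is not enough here, because such an analyte is nearly collinear with use.
3. Refit each declared marker with indicators for drug-class use and, where numbers allow, without users. Flag markers that do not persist, but do not discard them automatically.

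The cost is one CRF page, largely filled from the eligibility review already done, and one repeat analysis. Drug use is partly a proxy for severity, so the refit loses some precision and could hide true markers; it should stay a sensitivity analysis. Excluding users will often be thin in type I: at 50-60% use, 15 × 0.5 = 7.5 to 15 × 0.4 = 6 children would remain.
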